### Objectives and hypotheses

This study evaluates the impact of a combined nutrition counselling and an unconditional cash transfer RCT (SCC Trial), delivered on a mobile platform, on the level of empowerment of women in rural Bangladesh. This study will assess women’s experience of empowerment and disempowerment throughout the SCC trial.

The primary hypothesis is that in a community-based cluster RCT of a mobile phone-based nutrition BCC and unconditional cash transfer given to women in low-income families in rural Bangladesh, women’s empowerment will increase as measured by an increase in mean women’s empowerment scores (by an average percentage of 20) from the baseline to the end of the 24-month intervention, compared with women in the control arm.

The secondary hypotheses are that the mobile phone nutrition BCC and unconditional cash transfer compared to usual programmes will (1) increase control over income and economic resources, (2) improve input and decision-making power in nutrition and health care choices, and (3) decrease the acceptance and experience of IPV.

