### Study outcomes

The primary study outcome will be the difference in women’s empowerment scores in the intervention arm as compared with the control arm of the SCC Trial. Secondary study outcomes will include (1) control over income and economic resources, (2) input and decision-making power in nutrition and healthcare choices, and (3) experience and attitude towards IPV.

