### Sample size and power

The sample size for our trial is fixed by the primary hypothesis in the main SCC Trial, which estimated a total sample of 2184 mother–infant pairs from 104 clusters.^12^ We can find no reports of intracluster correlation coefficients (ICCs) for the women’s empowerment indicators we plan to use. Therefore, we estimate that the fixed trial sample size will provide at least 80% power to detect a 20% increase in women’s empowerment, assuming 30% of women are empowered and a high ICC of 0.2. Assuming a lower ICC of 0.05, we will have 90% power to detect a 13% increase in women’s empowerment.

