### Quantitative data

We will collect the women’s empowerment indicators in household surveys at the baseline and the endline of the 24 month study in the intervention and non-intervention arms. We will pretest all questions before the commencement of the study. We will use the validated short version of Marlowe-Crowne’s social desirability scale,^33^ which is based on a subset of 13 items from the original scale. We will calculate a social desirability score by adding up the number of socially desirable answers, out of the 13 questions. The potential range of the score will be from 0 to 13, and we will create three categories with a score of 0–4 graded as a low score, 5–9 as a medium score and 10–14 as a high score (online supplemental appendix table 3). The questionnaire assesses whether social desirability bias or the tendency of respondents to answer questions in a way viewed favourably by the research team has influenced the data collected. We will train the field researchers in detecting social desirability bias in qualitative data and limit bias by properly introducing the study to the respondents, building rapport and asking context-specific probing questions following the recent framework described by Bergen and Labonté.^34^ We will follow the process throughout the research.

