### Quantitative data analysis

Data analysis will be by intention to treat. The women’s empowerment composite index scores will be categorised as the percentage of women as empowered or disempowered. For each empowerment indicator, individuals are classified as adequate or inadequate based on Pro-WEAI predetermined thresholds. Women are considered empowered if four out of six indicators are adequate. We will also analyse impact of SCC intervention on individual indicators to assess increases or decreases in empowerment as not all indicators will respond or be impacted in the same way.

Analyses will be conducted at the mother–infant dyad level but will be adjusted for the cluster randomisation.^39^ Primary analyses will compare the prevalence of women’s empowerment at the end of the trial using Pearson’s χ^2^ tests and 95% CIs for the group difference, adjusted for clustering and generalised linear mixed models for non-continuous outcomes (eg, logistic mixed models for binary outcomes, for example, percentage of women’s empowerment). Models will include treatment group as a fixed effect, infants as a random effect to account for repeated measurements, and community cluster as a random effect to account for cluster effects. We will also assess if the women’s empowerment level at baseline, age, education, and presence or absence of a mother-in-law in the household modify the empowerment response to the intervention by testing for interactions between the intervention and these factors. STATA will be used for all analyses.

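### The primary endline comparison has no term for baseline empowerment, although it is measured in both arms; precision is given up, and the role of the infant random effect is unclear

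*Protocol article*

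**What the plan says.** Under Quantitative data the article says: "We will collect the women’s empowerment indicators in household surveys at the baseline and the endline of the 24 month study", in both arms. So every indicator in the composite is meant to have a pre-intervention value.

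Under Quantitative data analysis the primary contrast is at endline: "Primary analyses will compare the prevalence of women’s empowerment at the end of the trial". It is to be tested by a cluster-adjusted chi-squared test and by logistic mixed models. The terms are then given: "Models will include treatment group as a fixed effect, infants as a random effect to account for repeated measurements", plus a random effect for the community cluster. There is no baseline covariate, no time term and no treatment-by-time term.

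Baseline empowerment appears once, in the effect-modification sentence: "We will also assess if the women’s empowerment level at baseline, age, education, and presence or absence of a mother-in-law" in the household modify the response, tested by interactions with the intervention.

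The primary hypothesis, under Objectives and hypotheses, is worded as an "increase in mean women’s empowerment scores (by an average percentage of 20) from the baseline to the end of the 24-month intervention", compared with control. Study outcomes gives a between-arm difference in scores and does not mention change.

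**The concern.** Between-cluster variation is likely to dominate the error in this trial. Sample size and power reports no known ICC for these indicators and allows a value as high as 0.2. Randomisation is stratified by union, not by empowerment, so with 52 clusters per arm the arms can differ by chance in starting empowerment. A baseline measurement of the same construct is the natural covariate for removing part of that error. The plan collects it but does not put it in the primary comparison.

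The infant random effect adds a second difficulty. The quantitative empowerment survey has only two waves.

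- If the primary model uses endline alone, each woman contributes one binary outcome, and there are no repeated measurements for that effect to absorb.
- If baseline is meant to enter as a repeated outcome, the listed terms give one treatment coefficient across both waves. It would average a pre-intervention difference of zero in expectation with the endline effect.

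At stake are interval width, exposure to chance imbalance, and a possible later choice between adjusted and unadjusted results once baseline differences are known.

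**Working it through.** **Inputs.** From Sample size and power: "estimated a total sample of 2184 mother–infant pairs from 104 clusters", 30% empowered, ICC 0.2 or 0.05. That is 2184/104 = 21 per cluster, 52 clusters and 1092 women per arm. Two-sided alpha of 0.05 is assumed, in line with the planned 95% intervals. The baseline-to-endline correlation is not in the documents, so a range is shown.

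**The plan's own power figures.** Design effect = 1 + (21 − 1) × ICC.

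- ICC 0.2: design effect 5.0, effective n = 1092/5.0 = 218.4 per arm. 30% v 50% (the 20% read as points) gives 99.1% power; 30% v 36% (read as relative) gives 26.5%. The plan states at least 80%.
- ICC 0.05: design effect 2.0, effective n = 546 per arm. 30% v 43% gives 99.4%; 30% v 33.9% gives 28%. The plan states 90%.

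Neither stated figure is reproduced closely, although at least 80% is literally met if the increase is in points. Using 2080 or 2840 women gives the same picture. That is a separate matter; it is needed here only to judge what adjustment can change.

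**Where the error comes from.** At ICC 0.2 the between-cluster share of the variance of a cluster mean is 0.2/(0.2 + 0.8/21) = 0.84.

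**Unadjusted standard error.** For 30% v 43%, the difference that gives about 80% power at ICC 0.2: √[(0.3×0.7 + 0.43×0.57)/218.4] = √(0.4551/218.4) = 0.0456, or 4.6 points.

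**Effect of adjustment, closed form.** With r the baseline-to-endline correlation of cluster means, the variance is multiplied by 1 − r².

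| r (assumed) | 1 − r² | Detectable difference, 80% power, ICC 0.2 | Detectable difference, 90% power, ICC 0.05 |
|---|---|---|---|
| none | 1.00 | 12.9 points | 9.3 points |
| 0.2 | 0.96 | 12.6 | 9.1 |
| 0.3 | 0.91 | 12.3 | 8.9 |
| 0.5 | 0.75 | 11.1 | 8.0 |

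**Effect of adjustment, simulation.** The model was latent-normal with 21 women per cluster, 52 clusters per arm, ICC 0.2, a 13-point effect and 1500 trials per scenario. Cluster endline prevalence was regressed on arm, with and without the cluster's baseline value. The correlations are assumptions on the latent scale.

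| Between-wave correlation (cluster, woman) | SE unadjusted | SE adjusted |
|---|---|---|
| weak: 0.2, 0.1 | 4.6–4.7 points | almost unchanged |
| moderate: 0.5, 0.2 | about 4.6 | about 4.1–4.2 |
| strong: 0.8, 0.4 | about 4.6 | 3.2–3.3 |

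**Can adjustment rescue the relative reading?** For 30% v 36% at ICC 0.2 and r = 0.5, effective n = 218.4/0.75 = 291.2. The SE is √[(0.21 + 0.2304)/291.2] = 0.0389, so z = 0.06/0.0389 = 1.54 and power is Φ(1.54 − 1.96), about 34%. That is still far below 80%.

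**Change score.** Its variance factor is 2(1 − r): 1.6 at r = 0.2, 1.4 at r = 0.3, 1.0 at r = 0.5. It loses precision below r = 0.5, so the gain comes from covariate adjustment and not from analysing change.

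**Dilution if baseline is a repeated outcome.** With equal numbers at both waves and no treatment-by-time term, the treatment coefficient is roughly (0 + d)/2 = d/2. A true endline difference of 20 points would appear as about 10.

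**The case against.** The strongest reply is that a cluster-adjusted endline comparison is a valid intention-to-treat analysis. Chance imbalance between clusters is already in its standard error, and covariates are often settled in an analysis plan that is not shown here. The list of terms is not marked as exhaustive either; union, the stratification factor, is also absent. The validity point stands in full. The deferral point stands only in part, because the article names the model terms and gives baseline empowerment a different, specific role.

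Three stronger readings are tempting, and the documents do not support them.

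- A reader might infer that the intervals will be wrong or the result biased. They will not be: the interval is correct for its estimator, and randomisation protects the endline contrast in expectation.
- A reader might infer that the hypothesis of change from baseline goes untested. Under randomisation the endline difference and the difference in change have the same expectation. The real discrepancy is mean score in the hypothesis against percentage empowered in the analysis, and a baseline covariate does not resolve it.
- A reader might infer that the stated power hangs on this choice. It does not. Read as percentage points, power is already about 99%; read as relative increases, it is about 27% to 28%, and adjustment alone does not restore it.

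Two further cautions are fair. Strong correlation across about 24 months, from early pregnancy to child age 18 months, is only an assumption. The simulation also used a cluster-level baseline value and not the full proposed model. In a linear model with equal clusters, deviations from the cluster mean are orthogonal to arm, so the cluster mean carries most of the gain; unequal clusters and the logistic form were not examined.

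**Conclusion.** The point holds as a free improvement and a needed clarification. The listed primary model has no baseline term, the data for one are to be collected in both arms, and the only stated use of baseline empowerment is an interaction test. At ICC 0.2 the cost ranges from almost nothing under weak correlations, through about a tenth of the standard error (4.6 to 4.1 points) under moderate ones, to nearly a third (4.6 to 3.2 or 3.3) under strong ones. At ICC 0.05 the closed-form gain is 0.2 to 1.3 points in the difference detectable with 90% power, for r from 0.2 to 0.5. These sizes rest on assumed correlations.

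The infant random effect needs correcting whichever way it was meant. It is redundant with a single endline outcome, and without time terms it goes with a diluted treatment effect if baseline is a second outcome.

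**What to change.** Under Quantitative data analysis, state the following.

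- The primary model takes the endline outcome only as the response. It has treatment as a fixed effect and cluster as a random effect, and adjusts for the woman's baseline empowerment score (0–6 adequate indicators) and the cluster mean of that score.
- Missing baseline scores are handled by a simple prespecified rule, for example mean imputation with a missingness indicator. The rule should also cover indicator items that may not apply at enrolment, since the nutrition and health items include infant feeding and baseline falls in early pregnancy.
- The infant random effect is dropped for this outcome. If baseline is instead to be modelled as a repeated outcome, time and treatment-by-time terms are added, and the endline treatment contrast is named as the primary estimate.
- The effect is reported as a marginal difference in percentage points, so that it stays comparable with the sample-size section. The unadjusted cluster-adjusted comparison is supportive.

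The cost is a few sentences. No data, visits or participants are added. It should be fixed before endline data are seen by arm.

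### The mixed model's infant random effect for repeated measurements does not fit the endline comparison it serves: its variance is not identified, and with both waves the listed terms miss the endline effect

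*Protocol article*

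**What the plan says.** All the model text is in the protocol article, section Quantitative data analysis.

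- **Outcome.** It is binary: "Women are considered empowered if four out of six indicators are adequate".
- **Contrast.** "Primary analyses will compare the prevalence of women’s empowerment at the end of the trial". The same sentence names two methods: a cluster-adjusted Pearson chi-squared test with a confidence interval for the group difference, and generalised linear mixed models, logistic for a binary outcome.
- **Model terms.** "Models will include treatment group as a fixed effect, infants as a random effect to account for repeated measurements". A second random term covers the clusters. No time term, treatment-by-time term or baseline covariate is listed.
- **Baseline empowerment.** It appears only as a possible effect modifier: "We will also assess if the women’s empowerment level at baseline, age, education, and presence or absence of a mother-in-law in the household modify" (what these factors might modify is how women respond to the intervention).

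The section Quantitative data gives the measurement occasions: "We will collect the women’s empowerment indicators in household surveys at the baseline and the endline of the 24 month study". Participant recruitment and timeline likewise gives two. The primary hypothesis, in Objectives and hypotheses, concerns an increase "from the baseline to the end of the 24-month intervention, compared with women in the control arm".

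**The concern.** A random effect for repeated measurements needs more than one record per unit. The stated contrast uses the endline value alone, and each dyad has one such value. The listed model therefore does not match the listed comparison, and the text does not say which records enter.

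What is at stake is the odds ratio reported from the mixed model. On endline data it would depend on a variance that the data cannot determine. On both waves, with only the terms given, it would estimate neither the endline difference nor the change relative to control that the hypothesis describes.

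**Working it through.** **The plan's own figures.** The article gives no figure for the mixed model. Its power figures set the scale. The main trial "estimated a total sample of 2184 mother–infant pairs from 104 clusters", which is 2184/104 = 21 women per cluster and 1092 per arm. With design effect 1 + (21 − 1) × ICC, a two-sided 5% level (assumed, not stated) and increases read as absolute points from 30%:

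| ICC | Design effect | Effective n per arm | Comparison | Power | Article |
|---|---|---|---|---|---|
| 0.2 | 1 + 20 × 0.2 = 5 | 1092/5 = 218.4 | 30% v 50% | 99.1% | at least 80% |
| 0.05 | 1 + 20 × 0.05 = 2 | 1092/2 = 546 | 30% v 43% | 99.4% | 90% |

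The first figure is satisfied. The second is not reproduced, nor is it on a relative reading (28.1% for 30% v 33.9%). That is a separate matter, and nothing below depends on it.

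**Reading 1: endline records only.** There is one binary value per dyad. Write the log-odds as b0 + b1 × treatment + cluster effect + infant effect, with infant standard deviation s. Integrating out the infant effect leaves a probability that nearly the same cluster model reproduces for any s, with b1 rescaled. One simulated trial (104 clusters of 21, about 29% v 49% empowered at endline) with s held fixed gave:

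| s | −2 log-likelihood | Treatment log odds ratio |
|---|---|---|
| 0.01 | 2773.51 | 1.06 |
| 0.5 | 2773.55 | 1.11 |
| 1 | 2773.64 | 1.26 |
| 2 | 2773.74 | 1.71 |
| 3 | 2773.82 | 2.24 |

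The likelihood changes by 2773.82 − 2773.51 = 0.31, so the data cannot choose among these values. The odds ratio goes from exp(1.055) = 2.9 to exp(2.243) = 9.4.

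The test does not share this fault. In three further simulated endline datasets with s at 0.01, 1, 2 and 3, the likelihood-ratio statistic for treatment stayed within 25.20–25.26, 35.54–35.60 and 15.35–15.38.

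**Reading 2: both waves, listed terms only.** Randomisation makes the expected baseline difference zero. With two balanced waves and no time term, the expected treatment difference is (0 + d)/2, where d is the endline difference.

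- Risk difference: 20 points becomes 10, and 13 becomes 6.5.
- Marginal log odds ratio, 30% v 50%: 0.847 at endline. Pooled over waves it is 30% v 40%, or 0.442, and 0.442/0.847 = 52%.
- Fitted logistic mixed model, 60 simulated trials, true conditional log odds ratio 1.10: treatment-only mean 0.52 (48%); with time and treatment-by-time, the interaction averages 1.08 (98%).

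**The case against.** **The article does not say treatment is the only fixed effect.** It is the only one listed, and time terms are a detail that an article may leave to a fuller plan. This stands, and it makes the halving conditional. It does not rescue the endline reading: adding fixed effects does not identify a variance from one binary record per dyad.

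**A sound primary comparison is already there.** The cluster-adjusted chi-squared test with its confidence interval needs no infant term, and a model with treatment and cluster alone is estimable. This also stands. A reader might infer that the whole primary analysis is biased by half. The documents do not support that, because it requires stacking both waves without a time term and reading the result as the endline effect, against the stated endline contrast.

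**The power loss is moderate on the article's own pairings.** A reader might infer that power collapses. Under reading 2, take the variance of a two-wave mean as p(1 − p)(1 + r)/2 and assume a within-woman correlation r of 0 to 0.6. Power falls from 99% to 87–69% (20 points, ICC 0.2) and from 99% to 90–72% (13 points, ICC 0.05). Figures of 33–52% come from simulating 13 points at ICC 0.2 and 9.5 points at ICC 0.05, pairings the article does not use.

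**Infant or woman is mostly labelling.** The analysis is set at dyad level, so apart from multiple births the identifiers define the same groups. Accepted.

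**Baseline adjustment is optional.** An unadjusted endline comparison of randomised arms is valid. Accepted: the covariate is for precision, not validity.

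**Conclusion.** The point holds in limited form. Quantitative data analysis pairs an endline comparison with a random effect meant for repeated measurements and does not say which records enter the model. On endline data, the infant variance and the conditional odds ratio that depends on it are not identified; the treatment test and the chi-squared comparison are largely unaffected. On two waves with only the listed terms, the coefficient is about half the endline effect: exactly half as a risk difference when baseline prevalence is equal, and 48–52% on the log-odds scale in the cases worked.

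These sizes rest on simulated data with a baseline prevalence near the article's 30%. The odds-ratio range comes from a single simulated dataset and illustrates the problem; it does not predict the trial's result. The halving also assumes that no fuller plan adds time terms.

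**What to change.** State which waves enter the model, then choose one form.

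1. **Endline model (preferred, as it matches the stated contrast).** Fit the logistic mixed model to the endline outcome, one record per woman, with treatment group and baseline empowerment as fixed effects and cluster as a random effect. Delete the infant random effect.
2. **Two-wave model.** Use a woman or dyad random effect and a cluster random effect, add time and treatment-by-time, and define the endline contrast as the treatment effect.

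The cost is about two sentences in the analysis section. Baseline empowerment is already collected, so no new data are needed. The choice should be fixed before the outcome data are analysed.

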### Allocation of clusters

Our study site has over 1100 villages, which would be adequate to cover the anticipated sample size. Each cluster encompasses two to four villages and consists of ~1000 households and ~4500 population. We will use a fixed randomisation scheme to assign treatments to eligible clusters, with a uniform allocation ratio of treatments, stratified by union. The sample size will consist of 104 clusters, total women (n=2840) allocated to two parallel groups (n=1420) with 20 mother–infant dyads per cluster. Each cluster consists of one to four adjacent villages with a minimum population of 600 households per cluster with 454 villages in our study area for clustering. A subsample of the households from a purposively selected subset of clusters will be chosen for qualitative data.

The intervention and control groups will receive similar maternal and child health and nutrition services from the government, and the critical difference will be the nutrition BCCs with cash transfers on a mobile platform received by women in the intervention arm. The study design will control for potential observed and unobserved confounding factors as there will be an adequate number of clusters randomly allocated to the treatment groups. The geographical separation of clusters will limit the contamination of the intervention arm. We will use STATA V17 software to generate the random allocation sequence. We are unable to mask the treatment arm due to the nature of the intervention.

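### The treatment-by-factor interaction tests should name cluster-robust standard errors, because the cluster random effect as described does not cover factor effects that vary between clusters

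*Protocol article*

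**What the plan says.** Under Allocation of clusters, randomisation is by cluster: the trial will "assign treatments to eligible clusters, with a uniform allocation ratio of treatments, stratified by union". The same section gives the size: "The sample size will consist of 104 clusters, total women (n=2840) allocated to two parallel groups (n=1420) with 20 mother–infant dyads per cluster".

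Under Quantitative data analysis, the general statement is "Analyses will be conducted at the mother–infant dyad level but will be adjusted for the cluster randomisation". The model is then described: "Models will include treatment group as a fixed effect, infants as a random effect to account for repeated measurements", together with "community cluster as a random effect to account for cluster effects". The next sentence adds effect modification. It names the "women’s empowerment level at baseline, age, education, and presence or absence of a mother-in-law in the household" and asks whether these "modify the empowerment response to the intervention by testing for interactions between the intervention and these factors".

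All four factors are measured on the woman or her household. No separate model is given for the interaction tests, and no random slope, cluster-by-factor term or variance estimator is named.

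**The concern.** A treatment-by-factor interaction in a cluster-randomised trial is a between-arm comparison of factor effects estimated inside clusters. Each cluster yields, in effect, its own contrast, for example between women who live with a mother-in-law and those who do not. The interaction asks whether these contrasts differ on average between the two sets of clusters. Its error therefore has two parts: sampling error within clusters, and real variation of the contrast from one cluster to the next.

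A random cluster intercept describes differences in level. It largely cancels out of a within-cluster contrast, so it contributes little to the second part. The random effect for infants deals with repeated records on the same dyad and does not supply it either. If the factor effect does vary between clusters, the model-based standard error of the interaction is too small and its interval too narrow. Chance differences between clusters would then be reported as effect modification more often than the nominal rate.

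**Working it through.** **No figure to reproduce.** The article states no power, standard error or sample size for the interaction tests.

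**Inputs from the article.** There are 104 clusters, taken as 52 per arm under the uniform allocation ratio. Cluster size m is 2184/104 = 21 (Sample size and power) or 2840/104 = 27.3 (Allocation of clusters); the text also gives 20. Both 21 and 27 were carried. Prevalence of empowerment is 30%, with ICCs of 0.05 and 0.2 (Sample size and power).

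**Assumptions.** Two-sided 5% test; a binary factor with prevalence q of 40% or 50%; one record per woman; a true interaction of zero; a between-cluster SD τ of the factor's log odds ratio from 0 to 1.0. The article gives no value for τ.

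**Approximate formula.** Within one cluster, the variance of the factor's log odds ratio is about 1/[m·q(1−q)·p(1−p)]. For a difference of mean slopes between two arms of 52 clusters:

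- variance ignoring slope variation: (2/52) × 1/[m·q(1−q)·p(1−p)]
- true variance: (2/52) × {τ² + 1/[m·q(1−q)·p(1−p)]}
- ratio of true to model standard error: √(1 + τ²·m·q(1−q)·p(1−p))

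Take m = 21, q = 0.5 and p = 0.4 (midway between 30% and 50%). Then m·q(1−q)·p(1−p) = 21 × 0.25 × 0.24 = 1.26.

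- Model standard error: √(0.0385 × 0.794) = 0.175; simulated 0.185–0.186 at ICC 0.05.
- τ = 0.3: ratio √(1 + 0.09 × 1.26) = 1.06
- τ = 0.5: ratio √(1 + 0.25 × 1.26) = 1.15
- τ = 1.0: ratio √(1 + 1.26) = 1.50

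The simulated ratios at m = 21 were 1.02–1.03, 1.11 and 1.36–1.40. Direction and rough size agree, but the formula somewhat overstates, so the simulation is used for size.

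**Simulated type I error (%)**, random-intercept logistic model with model-based standard errors. Set 1: q = 40%, ICC 0.05 or 0.2, 2500 runs per scenario. Set 2: q = 50%, ICC 0.05 and 0.2, 1000 runs per cell. Set 3: q = 40%, ICC 0.1, 1200 runs per cell.

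| Slope SD τ | Set 1, m = 21 | Set 2, m = 21 | Set 2, m = 27 | Set 3, m = 21 or 27 |
|---|---|---|---|---|
| 0 | 4.6 | 5.5 | 4.6–6.4 | about 5.4 |
| 0.3 | 6.5 | 5.0–5.4 | 5.4–6.1 | 6.4–6.8 |
| 0.5 | 7.1–7.6 | 7.2–7.3 | 9.8 | 7.8–8.4 |
| 0.7 | 9.8 | – | – | 9.7–10.7 |
| 0.75 | – | 10.1–11.9 | 14.1–14.4 | – |
| 1.0 | – | 15.2–17.2 | 17.6–21.2 | – |

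Monte Carlo standard errors at 5%, from √(0.05 × 0.95/runs), are about 0.4, 0.7 and 0.6 points for Sets 1, 2 and 3. At τ = 0.3 the excess is at most small, and in Set 2 it cannot be told from nominal.

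**With the remedy.** Cluster-robust standard errors on the same intercept-only model gave 4.6–5.6% in Set 1 and 5.3–6.1% in Set 3. A refit under Set 2 conditions (ICC 0.05; τ = 0, 0.5 and 1.0; 400 runs per cell, Monte Carlo error about 1.1 points) gave 2.8–6.0% with robust standard errors and 2.8–5.5% with a random slope. Intercept-only gave 4.8–20.5% in the same refit.

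**The case against.** The strongest reply is that the article does not commit to the faulty analysis. It never writes that the cluster effect is an intercept only, never says that the interaction models keep exactly the main-effect structure, and never says that standard errors will be model-based. It promises in general terms to adjust for cluster randomisation. A condensed article may leave random slopes or a variance option to the analysis plan, and a robust variance would remove the problem. This stands. A reader might infer that the plan fixes an intercept-only model with model-based standard errors; that is the ordinary reading of the text, but still an inference.

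A reader might also infer that the interaction p values are too small as a matter of course. They are too small only if factor effects vary between clusters, and the article gives no figure for that. A slope SD of 0.7 means that the factor's odds ratio differs from its typical value by up to exp(1.96 × 0.7) = 3.9-fold either way across 95% of clusters; nothing in the article supports so much. On the other side, ICCs of 0.05 to 0.2, read on the latent logit scale, imply intercept SDs of √(ICC/(1−ICC) × π²/3) = 0.42 to 0.91. An SD of 0.5 is thus not large beside the variation in level that the article itself allows. That concerns level and not slope, so it shows plausibility only.

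The simulations are also simpler than the described model: one record per woman and a single binary factor, whereas the plan includes an infant random effect and factors such as age and education. The mechanism does not depend on these features, but the exact percentages do.

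**Conclusion.** The point holds conditionally. As described, the interaction tests rest on a cluster random effect that is ordinarily an intercept, while treatment is assigned by cluster and the factors vary between women within clusters. If a factor's effect varies between clusters, model-based standard errors for these interactions are too small. Under assumed slope SDs, type I error is about nominal at 0, roughly 5–7% at 0.3, 7–10% at 0.5 and about 10–11% at 0.7. It is higher still at larger SDs, for which the article offers no support.

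Three stronger readings are not supported:

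- The primary treatment comparison is not affected. The point concerns only the interaction standard errors.
- No familywise error rate should be claimed for the four tests together. It would require independent tests with a common slope SD, and most of any such total would be ordinary multiplicity.
- The tests should not be presented as deciding for whom the intervention works. They are additional analyses and appear in neither Objectives and hypotheses nor Study outcomes.

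This is a low-priority, inexpensive improvement and not a demonstrated error.

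**What to change.** In Quantitative data analysis, after "modify the empowerment response to the intervention by testing for interactions between the intervention and these factors", add: *using cluster-robust standard errors with the community cluster as the unit*. A random slope of the factor by cluster is an acceptable alternative. Leave the main-effect model as it is.

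The cost is one clause and no new data; with 104 clusters the robust variance performed well. Interaction intervals become slightly wider when factor effects vary between clusters. When they do not, there was no detectable penalty: 4.6% against 4.6% in Set 1, and 6.0% against 5.8% in the refit at 21 women per cluster. If robust standard errors or random slopes are already intended, the clause simply puts that on record.
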